### Size of the study population

For the cohort study 300 patients with COPD will be recruited. This number is based on the calculated sample size for the RCT part of the study. The sample size calculation for this RCT is based on the identification of a minimal relevant clinical difference in exacerbation frequency between the experimental and the control group. The difference in exacerbation rate is expected to be 22% (based on exacerbation rates found in previous studies with rehabilitation programmes) [37,38]. The probability that the study will detect a treatment difference is 80% at a two-sided 5% significance level. This is based on the assumption that the intervention period will be 12 months, the follow-up period will be 24 months and the ratio control subjects to intervention subjects is 1:1. A sample size calculation for comparing event rates between two independent groups is used, resulting in 79 participants per group [39,40]. Assuming outcome data will be analysed prospectively and considering a drop-out rate of 20%, 100 patients per group will be needed in this two treatment parallel-design study.

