#### *Primary outcome measure*

The primary outcome measure will be exacerbation frequency, calculated as the number of COPD exacerbations experienced by the patient in a post exacerbation period of two years. A COPD exacerbation will be identified as a sustained worsening of the patient’s condition occurs from the stable state and beyond normal day-to-day variations that is acute in onset and may warrant additional treatment [45]. A recurrent exacerbation will be defined as a subsequent occurrence; exacerbations are assumed to be independent of each other. The follow-up period is twelve months (twenty-four months for the long-term outcome measurement) to overcome time confounding, since exacerbation frequency is seasonal and particularly related to influenza and other viral epidemics [45].

In the cohort, exacerbations will be identified by means of an event based approach, whereas in the RCT exacerbations will be identified by means of an event based approach (health care contact) and symptom based approach (clear increase of respiratory symptoms). Usual assessment of exacerbations is done by recording health care contacts. However, there are many underreported exacerbations in COPD patients when using this event based method [46]. On average, these underreported exacerbations have similar severities to reported exacerbations [45]. Therefore, increase of respiratory symptoms will also be recorded in the RCT. When measuring the appearance of exacerbations with these two methods, this trial is able to compare event based and symptoms based methods in relation to the primary and some of the secondary outcome measures.

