### Data analysis

#### *Clinical effectiveness*

The descriptive characteristics are presented quantitatively as mean (±standard deviation) or median (5^th^ - 95^th^ percentile), depending on the data distribution, whenever the variable is continuous or as a percentage whenever the variable is dichotomous or categorical. Data will be analysed with SPSS-19. Assumptions accompanying the following statistical methods will be checked and all data analyses will be applied by a blinded analyst.

Data from the RCT will be analysed to examine intervention main effect on the counts for the primary outcome (exacerbation frequency) and the secondary outcomes. All exacerbations from each patient will be used as the dependent outcome to evaluate the effect of physical therapy at the end of the intervention (12 months) and follow-up (24 months). Measurement moments for secondary outcomes are baseline, three and six weeks, three, six, twelve and twenty-four weeks. The effects of the variable of primary interest, physical therapy (pdPT), will be analysed in a generalized linear model (GLM) for group (intervention vs. control) analysis of covariance with adapted regression for count data distribution. Analyses of secondary outcomes will be done with linear regression analysis and generalized linear models. Since exacerbation outcome in the RCT is measured with two methods, analyses will be based on the event-based approach, on the symptom-based approach and on a combination of both. Potential confounding by variables like, age, gender, GOLD stage, smoking, physical activity in daily life, exacerbation history, severity of latest exacerbation, and comorbidity, will be controlled for. Results from a ‘per-protocol’ and an ‘intention-to-treat’ principle will be compared. At a minimal statistical power of 80%, p-values smaller than 0.05 will be considered as significant.

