## Discussion

In this article the protocol of a cohort-nested randomised controlled trial is presented, concerning a study about the effect and cost-effectiveness of standardised physical therapy as a supportive measure to prevent or postpone future exacerbations, to shorten the duration or to decrease the severity of future exacerbations in COPD patients experiencing acute exacerbations. The focus on prevention of exacerbations by means of physical therapy fits one of the prime management goals for COPD, which is ‘reducing the frequency of hospitalisations due to exacerbations’ [1]. It is expected that the outcomes of this study will provide useful information about the effects of physical therapy on exacerbations, which may alter the role of physical therapy in managing COPD in the future.

Healthcare utilisation is not an optimal substitute for exacerbation frequency, exacerbation duration and exacerbation severity, depending on many unrelated social factors and comorbidity. It is an outcome in its own right [45]. Therefore, not only will this event based approach be applied in this trial, also a symptom based approach will be used. Both approaches will be used separately and together and their influence on outcome will be compared during statistical analyses.

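### The single primary outcome is analysed under three unranked exacerbation definitions at 12 and 24 months, each at p<0.05, and the protocol contradicts itself on the primary period

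*Protocol article*

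**What the plan says.** **Sample size.** The section Size of the study population plans for one comparison: "The probability that the study will detect a treatment difference is 80% at a two-sided 5% significance level". The result is 79 per group, raised to 100 for 20% drop-out. The section does not say which exacerbation definition the expected 22% difference refers to.

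**Outcome.** The section Primary outcome measure names exacerbation frequency alone, "calculated as the number of COPD exacerbations experienced by the patient in a post exacerbation period of two years". The same paragraph then gives the follow-up period as twelve months, with 24 months as the long-term measurement.

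**Analysis.** Under Clinical effectiveness, all exacerbations are used "to evaluate the effect of physical therapy at the end of the intervention (12 months) and follow-up (24 months", and "analyses will be based on the event-based approach, on the symptom-based approach and on a combination of both". Per-protocol and intention-to-treat results are to be compared. One rule covers everything: "p-values smaller than 0.05 will be considered as significant". The Discussion confirms how the definitions will be used: "Both approaches will be used separately and together and their influence on outcome will be compared during statistical analyses".

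No definition is ranked above the others, and no testing order or adjustment is given.

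**The concern.** A trial planned around one 5% test keeps its error rate only if one analysis carries the conclusion. Here three versions of the same outcome, at two horizons, face the same threshold, and nothing says which one answers the trial's question. If one version is significant and the others are not, the text does not stop a claim of benefit on that version and gives no rule for settling the matter.

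The text also offers no safe default. The event-based definition is listed first, but the protocol says it misses many exacerbations, and the Discussion calls healthcare utilisation a less than optimal substitute for exacerbation frequency. For the period, a reader can find support for either 24 or 12 months within one paragraph.

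**Working it through.** **1. The plan's own figure.** The drop-out step is consistent: 79 / (1 − 0.20) = 98.75, so 99, rounded up to 100. The 79 cannot be reproduced uniquely, because no base rates are given and the 22% is not said to be absolute or relative. It is compatible with a single test. If 22% is read as an absolute difference between proportions, n = [1.96·√(2p̄(1−p̄)) + 0.842·√(p₁(1−p₁) + p₂(1−p₂))]² / 0.22². This gives 77 to 80 per group when the higher proportion lies between 0.51 and 0.71; for example, 0.60 against 0.38 gives 80. Nothing in the figure allows for more than one test.

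**2. Number of tests.** From the text: 3 definitions × 2 time points = 6. If the two-year period is accepted as the designated one, 3 remain.

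**3. Upper bound.** For k independent tests the chance of at least one p<0.05 under the null is 1 − 0.95^k:
- k = 3: 14.3%
- k = 6: 26.5%

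The tests share patients and events, so these bounds are too high to quote as the size of the problem.

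**4. Allowing for overlap.** The test statistics are treated as equally correlated standard normals, with correlation ρ assumed, and the chance that any |Z| exceeds 1.96 is computed:

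| Assumed ρ | 3 definitions, one time point | 3 definitions, both time points |
|---|---|---|
| 0.6 | 11.8% | 18.7% |
| 0.7 | 10.9% | 16.4% |
| 0.8 | 9.8% | 13.9% |
| 0.9 | 8.4% | 10.8% |

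**5. Cross-check with counts.** Null trials were simulated with overdispersed counts: 79 per arm, 20,000 trials per scenario, ten scenarios. In each, some exacerbations met both definitions and others only one. The event rate (1.5 per year), the dispersion (0.3 or 0.7) and the share meeting both definitions (20–60%) are assumptions. Chance of at least one significant result:
- one pre-named test: 4.9–5.3%
- three definitions at one time point: 7.6–10.8%
- three definitions at both time points: 11.5–16.2%

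The simulated correlation between the event-based and symptom-based statistics at 24 months was 0.57–0.91, close to the range used in step 4.

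**The case against.** **The definitions are there to be compared.** The protocol presents two ways of recording exacerbations as a chance to compare methods, and nowhere says that any one significant version proves efficacy. A reader might infer an any-one-wins rule, but the text states none. This stands. The defect is that the text does not exclude such a claim while applying one threshold to every version.

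**A period is named.** It would be wrong to say that no time point is designated, since the outcome is first defined over two years. This stands too. The fault is the contradiction with twelve months in the same paragraph, and the reader who accepts 24 months is left with the three-test figures.

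**Twelve tests.** A reader might double the count by adding the per-protocol population. The protocol says only that the two sets of results are compared, which reads naturally as a sensitivity check, so a twelve-test error rate is not supported.

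**Expected disagreement.** Under-reporting of events predicts different counts by definition. It does not by itself predict different treatment effects, so the protocol cannot be said to expect conflicting results.

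**Direction.** The percentages are two-sided. A false claim of benefit is half of each: for three definitions about 4–6%, against a nominal 2.5%. The relative inflation is the same.

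**Condensed article.** A multiplicity procedure may sit in an analysis plan that is not shown, and its absence here is no finding. But the definition and period that carry the primary conclusion belong with the outcome and sample size, and this text addresses both: it lists three definitions under one threshold and gives two periods.

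**Conclusion.** The point holds in a limited form. One primary outcome, sized for one two-sided 5% test, is analysed under three unranked definitions at two time points with every p<0.05 called significant, and the primary period is stated in two incompatible ways.

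The part that survives every objection is three definitions at one time point: about 8–12%, roughly double the stated 5%. With both time points it is about 11–19%. Both ranges rest on assumed correlations of 0.6–0.9; higher correlation brings them nearer to 5%, lower correlation raises them.

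**What to change.** Before any data are seen by arm, the sponsor should:

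1. Name one exacerbation definition as confirmatory and justify it. The choice is the sponsor's, since the protocol itself lists weaknesses of the event-based count. If the combined definition is chosen, the rule for combining must be written down.
2. Reconcile the Primary outcome measure section to one primary period, 12 or 24 months, and use the same period in the sample size and analysis sections.
3. State that the trial's conclusion rests on that analysis, by intention-to-treat, at two-sided 5%.
4. Label the other definitions and the other time point secondary or supportive, and per-protocol a sensitivity analysis. The event-based section itself notes that an exacerbation may explain missed therapy appointments, so a per-protocol set could be selected on the outcome.

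The cost is a few sentences and the loss of the option to claim success on a supportive version. No extra data or patients are needed, and the 79 per group is unaffected by this point.

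Keeping all three definitions as confirmatory would cost more. With Bonferroni each is tested at 0.05/3 = 0.0167, and the required size grows by (2.394 + 0.842)² / (1.960 + 0.842)² = 10.47 / 7.85 = 1.33. That gives 79 × 1.334 = 105.4, so 106 per group, or 106 / 0.8 = 132.5, so 133 after drop-out. Staying at 79 would leave about 66% power per test.

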#### *Economic evaluation*

From the RCT data cost-effectiveness and a cost-utility of physical therapy in COPD patients experiencing exacerbations compared to usual care will be established using a one and two year time horizon.

A cost-effectiveness analysis will be performed, weighing incremental costs against the mean incremental effect in terms of quality of life based. For assessing patient outcome, the score of the disease specific quality of life measures CCQ and CRQ-SR will be used at the 12 months follow up moment. For this purpose, a societal perspective will be administered, indicating the relevance of direct medical, direct non-medical and indirect costs, as adding measurement of indirect costs will provide a more comprehensive picture of the burden of exacerbations [55]. For defining the content of care ‘consumed’, out of pocket costs, lost productivity costs and direct non-medical costs for each patient in the RCT, resource use will be measured using patient questionnaires. These frequently used retrospective questionnaires will cover a three months retrospective period. Moreover, patients’ daily diary cards will be assessed, to incorporate each exacerbation experienced by a patient that involves ‘consumed’ care. The costs of the experimental physical therapy will be assessed using micro-costing and time-and-motion techniques in several participating practices and patients’ dossiers of the physical therapist will be assessed.

For the cost-utility analysis, quality adjusted life year (QALY) will be calculated based on the EuroQol questionnaire (EQ-5D-3L). The EQ-5D-3L is a generic quality instrument that will make it able to calculate utilities at each outcome measurement (on a 12 months’ and 24 months’ basis). Thus, societal cost will be used to calculate the incremental cost-effectiveness based on CCQ and CRQ-SR and to calculate the incremental cost-utility based on QALYs. Besides, the cost of the physical therapy intervention will be assessed against the incidence of exacerbation in both groups within the RCT.

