### Study design

A cohort-nested, prospective, randomised controlled trial (cohort-nested RCT) will be conducted. This means that a RCT will be embedded within a COPD cohort (Figure 1). The cohort will consist of COPD patients who receive usual multidisciplinary COPD care and guideline-directed physical therapy (gdPT). The cohort will serve as an optimal recruitment population for the RCT to show the surpassing importance of physical therapy interventions on exacerbations. Therefore, a RCT that holds a large contrast of protocol-directed physical therapy (pdPT) versus sham treatment (ST) will be constructed. This means that when patients from the COPD cohort report an exacerbation, with an occurrence no longer than 56 days ago (a trade-off between threshold values of 35–91 days in which the majority of exacerbations have returned to baseline [36]), they are either randomised to the experimental group (protocol-directed physical therapy (pdPT)) or the control group (sham-treatment (ST)). This RCT will be used to study effectiveness of physical therapy in addition to an economic evaluation.

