### Cohort

All participants in the cohort receive usual multidisciplinary COPD care including guideline-directed physical therapy. In the Netherlands usual COPD care is given by a pulmonologist and/or a GP. This usual COPD care entails lung function testing, medication prescription for COPD and counselling, including education about the disease, symptoms and risks and tailor-made advice, which basically comes down to two major aspects; stop smoking and increase physical activity in everyday life [41]. In the light of the latter, all patients in the cohort are referred for usual physical therapy and physical activity advice. Usual physical therapy in the Netherlands is guideline-directed physical therapy (gdPT), provided by registered physical therapists and based on the KNFG physical therapy guidelines for COPD [35]. These guidelines provides assistance for applying physical therapy intervention (diagnosis and treatment) in COPD patients coping with impairments in mucus clearance, pulmonary function, muscle function and exercise capacity, and with limited physical activities due to dyspnoea or exercise intolerance. In the guidelines the effectiveness of several treatment modalities (specifically exercise training, breathing exercises, peripheral and respiratory muscle training) was reported and evidence based recommendations for the application of these modalities in physical therapy programmes were made. Moreover, disease management strategies are integrated. Short term goals incorporate improvement of patient’s knowledge, self-management and confidence to accomplish activities. Medium term goals are relief of dyspnoea, improvement of impaired airway (mucus) clearance, and improving or retaining exercise performance and physical activity in everyday life [35]. Long term goals entail improvement or preservation of disease related quality of life. Physical therapists are free to compile a patient-centred program at one’s professional discretion, within the limitations of the guideline. Hence, frequency of the guideline-directed physical therapy for COPD in the Netherlands varies; patients visit their physical therapist generally one to three times a week, for one hour, ranging from one-time consultation to multiple consultations during 3–12 months, depending on disease severity (based on usual care given in participating physical therapy practices) (Table 1).

**Table 1 T1:** Contrasts between RCT experimental and control group and cohort

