	** *Intervention* **	** *Content* **	** *Intensity* **	** *Frequency* **	** *Start* **
Cohort	**Guideline-directed physical therapy (gdPT):**	One or more of:	Ranging on the full intensity scale	On average:	
		Exercise training, peripheral muscle strength training, respiratory muscle training, breathing exercises, electrical muscle stimulation, physical activity in daily life (homework)		30 minutes to 1 hour	
	A programme made by individual PTs, within the limitations of the KNFG physical therapy guideline for COPD (usual care)				
				1 to 3 times a week	
				During 3 months to multiple years	
RCT experimental group	**Protocol-directed physical therapy (pdPT):**	Both exercise training and peripheral muscle strength training;	Endurance/ interval training ≥ 60% of (sub) maximum, muscle strength training ≥ 80% of maximum, always: borg-scale ≥5	Minimal:	*Early* PT: starting within 56 days after an acute exacerbation
				1 hour	
	A complete programme by protocol, according to the KNGF physical therapy guideline for COPD, but with strict conditions			Twice a week	
		When indicated: respiratory muscle training, breathing exercises, electrical muscle stimulation		During 12 months	
		Always: physical activity in daily life (homework)			
RCT control group	**Sham-treatment (ST):**	One-time consultation: advice to be physically active in daily life			
	No physical therapy				
	*Or*				
				Maximal:	
	Very low-intensity exercise training	Exercise training only	Endurance/ interval training ≤ 15% of (sub) maximum or borg-scale ≤2	30 minutes	
				Once a week	
				During 12 months	

Definition of abbreviations: RCT = randomised controlled trail; COPD = chronic obstructive pulmonary disease; KNGF = the Dutch Society for Physical Therapy.

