#### *Control group*

Patients in the control group receive sham-treatment (ST), which entails no or very low-intensity exercise training, for one year. The latter applies only if the participant in the control group insists on training in a physical therapy practice. The very low-intensity exercise training is limited to a maximum of 30 minutes once a week, with an intensity of 15% or lower of (sub) maximum physical exertion, based on the results of a maximal CPET and six-minute walk test. In addition, ratings of perceived exertion and dyspnoea of two or lower on the modified Borg-scale (0–10) are used to tailor exercise intensity [42]. There will be no further peripheral muscle strength training, respiratory muscle training, breathing exercises nor electrical muscle stimulation [35]. Furthermore, patients will be advised to do at least 30 minutes moderately intense physical activity on their own for at least five days a week according to the physical activity norm [43].

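### The economic evaluation names usual care as comparator, but the randomised control arm gets sham-treatment, so the trial's ratio would carry the wrong label

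*Protocol article*

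**What the plan says.** The Economic evaluation section fixes both the data source and the comparator: the RCT data are to give cost-effectiveness and "cost-utility of physical therapy in COPD patients experiencing exacerbations compared to usual care will be established using a one and two year time horizon". Cost-effectiveness and cost-utility are also part of the stated Study aim.

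Usual care is described under Cohort: "All participants in the cohort receive usual multidisciplinary COPD care including guideline-directed physical therapy". The same section adds: "Usual physical therapy in the Netherlands is guideline-directed physical therapy (gdPT), provided by registered physical therapists". The Abstract likewise places gdPT inside usual care. In Table 1 the gdPT entry reads "A programme made by individual PTs, within the limitations of the KNFG physical therapy guideline for COPD (usual care", and it stands in the cohort row only.

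The trial comparison is a different one. Under Study design, "a RCT that holds a large contrast of protocol-directed physical therapy (pdPT) versus sham treatment (ST) will be constructed". Under Control group, "Patients in the control group receive sham-treatment (ST), which entails no or very low-intensity exercise training, for one year". That section also excludes strength training, respiratory muscle training, breathing exercises and electrical stimulation for controls.

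**The concern.** An incremental cost-effectiveness ratio has meaning only relative to its comparator. The section names one comparator, while the randomised arms supply another. Both the incremental cost and the incremental effect of pdPT against little or no training may differ from those against the physical therapy that Dutch patients with COPD ordinarily receive. If the result is reported under the stated label, it will appear to answer whether the strict programme is worth adopting in place of current practice. The trial does not randomise that question.

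**Working it through.** The protocol states no figure for this point, so there is none to reproduce. The check has two parts.

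**1. Who receives what**

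| Group | Physical therapy | Called usual care? | In the RCT? |
|---|---|---|---|
| Cohort | gdPT | Yes (Abstract, Cohort, Table 1) | No |
| Experimental | pdPT, by strict protocol | No | Yes |
| Control | ST: one consultation, or very low-intensity training | No | Yes |

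Neither randomised arm receives what the protocol calls usual care. The Economic evaluation section measures resource use for RCT patients and ends by relating cost to exacerbations in the two RCT groups. It describes no comparison with the cohort. Its data can give pdPT against ST and nothing else.

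**2. Does the comparator matter? An illustration in contact hours**

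Formula: hours = sessions per week × hours per session × weeks. Assumptions: a 52-week treatment year, 13 weeks for three months, full attendance, and 1 hour for a single consultation (its length is not given).

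- pdPT (Experimental group): 2 × 1 × 52 = 104 h.
- ST, lower end (Table 1, one consultation): 1 h.
- ST, upper end (Control group, 30 minutes weekly): 1 × 0.5 × 52 = 26 h.
- gdPT, lowest (Cohort, one-time consultation): 1 h.
- gdPT, short course (Table 1, weekly 30-minute sessions for three months): 1 × 0.5 × 13 = 6.5 h.
- gdPT, upper end (Cohort, three one-hour visits weekly for 12 months): 3 × 1 × 52 = 156 h.

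Increment of pdPT:

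| Comparator | Smallest | Largest |
|---|---|---|
| ST | 104 − 26 = +78 h | 104 − 1 = +103 h |
| gdPT | 104 − 156 = −52 h | 104 − 1 = +103 h |

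With the 6.5-hour gdPT course the increment is 104 − 6.5 = +97.5 h. The sign turns negative only when gdPT exceeds 104 h. At three one-hour visits a week that takes more than 104 / 3 = 34.7 weeks, which lies within the stated range of up to 12 months.

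**The case against.** The strongest reply is that this is a labelling slip. The Abstract sets pdPT against ST and embeds the economic evaluation in that trial, and the Economic evaluation section itself starts from RCT data. The pdPT-versus-ST ratio is evidently what will be computed, and correcting the label changes no data collection, costing or utility step. This stands. A reader might infer that the economic evaluation cannot be estimated at all. The documents do not support that; only the ratio against usual care is out of reach.

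A second reply is that usual care here means GP and pulmonologist care without physical therapy, which ST would resemble. There is some support for this. The Cohort section uses separate terms for usual COPD care and usual physical therapy, Study design lists the two side by side, and the Economic evaluation section contrasts physical therapy in general with usual care. But the Abstract and the Cohort section say that usual care includes gdPT, the Cohort section says all cohort patients are referred for usual physical therapy, and Table 1 attaches the label to gdPT. On balance these outweigh it.

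A third reply concerns size. The −52 h sets the longest and most frequent gdPT course within a year against pdPT at what Table 1 calls its minimum, and no typical gdPT dose is given. Contact hours are also only one part of the planned societal cost. Both points stand. A reader might infer that total incremental cost changes sign between the two comparators, or that payers will be misled. The documents show neither: the first would need cost data, and the second depends on how the results are reported.

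**Conclusion.** Wrong as written. The comparator named for the economic aim is not the one randomised. The RCT supports an incremental ratio of pdPT against sham-treatment; it gives none against usual care as the protocol describes it.

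This conclusion comes from comparing the sections and rests on no calculation. The hours only illustrate that the comparator matters: the therapy-input difference is always positive against ST (+78 to about +103 h) but runs from −52 to about +103 h against gdPT, under the attendance and consultation-length assumptions given. They say nothing about the sign or size of the difference in total societal cost.

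**What to change.** Reconcile the Economic evaluation section with Study design, Cohort, Table 1 and Control group. In the Economic evaluation section, replace the reference to usual care with sham-treatment (no or very low-intensity exercise training). Add one sentence stating that the RCT gives no randomised cost-effectiveness or cost-utility estimate against guideline-directed usual care.

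The cost is one or two sentences. Arms, measurements, sample size and calculations stay as they are. The economic claim becomes narrower: it describes the strict programme against little or no physical therapy, not against current Dutch practice.
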